In the recent years, Direct Acting Antiviral therapy with proven efficacy in the general population and very limited side effects have been approved [26]. These new treatments offer the possibility of re-evaluating the SMD population for administering the new treatments to the patients who did not tolerate previous treatments.

Protocols of mental health services do not usually include routine screening for HCV, which may remain underdiagnosed and untreated [6]. In addition, HCV infection may remain active in SMD patients [21].

Nielsen et al. proposed the implementation of programs for the management of mental and physical illnesses in SMD patients coordinated by a multidisciplinary team. The purpose of these programs is to optimize treatment outcomes and reduce dropout rates [27]. Most collaborative management programs have been endorsed by associations related to mental health, diabetes, and cardiology [28].

Several studies have analysed the effectiveness of mental health nurse-led interventions in addressing many of the challenges that standard management models are unable to address. Thus, forty clinical trials evaluating nurse-led multifaceted interventions have been identified in a scoping review; many of them were aimed at assessing treatment adherence and medication management in patients with psychosis and schizophrenia [29]. As educators and counsellors, mental health nurses address barriers to adherence by using shared decision-making techniques and tools, which engage and empower patients to actively participate in decisions about their treatment [30]. These skills could be applied to improve treatment adherence, medication management, and transitional care in different healthcare settings, such as in patients with psychosis and concomitant HCV infection. The therapeutic relationship that mental health nurses build with these patients and their families is also an advantage to improve both treatment adherence and user satisfaction [31, 32].

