##### Endpoints and measures

The cure rate and adherence to treatment will be the primary endpoints. To assess cure, HCV viral load will be determined 8–12 weeks after the end of treatment. Patient adherence to treatment will be evaluated using the AIDS Clinical Trials Group method. By this method, patients are inquired about medications not taken in a period of four days prior to the interview: % adherence = (total galenic units prescribed for that period—total units not taken) / total galenic units prescribed for that period [40]. The cut point for this measure has been set to 95%, as the best threshold for a predictive positive virologic response in patients with HIV [41]. A record will also be kept of whether the patient needed to use a pillbox to ensure medication intake and/or required monitoring by the family or the mental health unit to guarantee the correct use of the treatment.

Secondary endpoints include sociodemographic and clinical data and data related to the healthcare process. Other variables in relation to the patient include changes in daily functioning as assessed using the Life Skill Profile (LSP) [42]; negative symptoms, measured on the Positive and Negative Syndrome Scale (PANSS) [43]; and changes in quality of life, measured with the Euroqol5D Health Questionnaire [44], all of them in their Spanish version (See Table 1). These questionnaires will be administered by an evaluator (psychologist or nurse) trained for it and blind to the experimental condition assigned to each patient.

**Table 1 Tab1:** Psychometric characteristics of the instruments included

Questionnaire	Domain (s)	Psychometric properties
**Life Skill Profile (LSP)** [42]	Self-care	Concurrent validity, this scale was compared with the social behaviour schedule SBS: 0.56 Interrater reliability *r* = 0.62, and internal consistency α = 0.82
	Interpersonal social behaviour	Concurrent validity, this scale was compared with the social behaviour schedule SBS: 0.54 Interrater reliability *r* = 0.69, and internal consistency α = 0.77
	Communication and social contact	Concurrent validity, this scale was compared with the social behaviour schedule SBS: 0.63 Interrater reliability *r* = 0.86, and internal consistency α = 0.86
	Non-personal social behaviour	Concurrent validity, this scale was compared with the social behaviour schedule SBS: 0.36 Interrater reliability *r* = 0.76, and internal consistency α = 0.78

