Regarding healthcare process indicators, the number of previously detected but untreated cases, detection rate after screening the SMD population, percentage of detected cases referred to the digestive service, and delay time until first consultation with the specialist will also be recorded. In addition, scheduled and unscheduled visits led by the monitoring team and number of calls made and received by this team will be recorded. Regarding hepatitis, case classification by genotype and treatment administered will also be recorded. In addition, the prevalence of undiagnosed HCV infection and diagnosed but untreated HCV infection in SMD patients will also be estimated. Finally, a comparison of daily life functioning, occurrence of symptoms, quality of life, and frequency of adverse events during active infection and once cured will be performed.

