#### Monitoring

During the treatment period (8–12 weeks depending on the prescribed drug), actions will be taken to ensure correct treatment adherence. To such purpose, the mental health nurse will assess patient’s ability to comply with the treatment. In case of patient’s inability, the nurse will assess family’s commitment to supervise and remind the patient about drug intake. In both cases, the nurse will carry out an educational intervention to ensure that the patient and/or their family clearly understand treatment guidelines. This intervention is structured through a standardized care plan. In cases in which proper treatment use is not guaranteed, medication will be provided weekly by the monitoring team.

Upon completion of the 8–12 weeks treatment period, a final evaluation of all patients will be performed. The data collected in this evaluation visit include adherence to treatment, person responsible for treatment administration, occurrence of adverse effects or interactions, and number of visits and calls during the treatment period.

A third and final analysis of all study variables will be carried out six months after starting the treatment. Finally, disappearance of the viral load and, therefore, cure from HCV will be determined by a new blood test.

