#### Ethics

This study was approved by the Malaga Provincial Research Ethics Committee with the code CQG-20 (0444-N-20). This study will comply with best clinical practice guidelines and the ethical standards for research involving human participants established in the Declaration of Helsinki and its subsequent versions.

Clinical data will be processed in accordance with current legislation on data protection.

In the preliminary phase of the study, consisting of a screening of the entire population diagnosed with a serious mental disorder, only verbal consent is being requested. This blood analysis has been included as part of the annual physical health review offered to patients with severe mental disorders in the Unit, which already involves blood extraction, and the Ethics Committee has approved that written consent is not required when treating of a screening of the entire population.

However, people who finally have a positive viral load (which will predictably be a small percentage of the previous ones) will be offered to participate in the clinical trial, for which they must give their informed consent in writing.

Prior to inclusion in the trial, each subject will be informed in writing and orally of the objectives and methodology of the project. Informed consent will be required for inclusion. If the patient is not legally competent, informed consent from the legal guardian will be required by nursing staff.

Adequate medical assistance will be provided in case patients experienced any adverse event. All patients will be informed of the need for medical assistance for concomitant illnesses of which the research team is aware.

The occurrence of adverse events will be monitored during the study by the Gastroenterology Service (Ward) as part of routine monitoring of HCV patients, in accordance with the effects described in the technical sheet of the medication prescribed to each patient.

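### Comparing adverse-event frequency during active infection with that once cured mixes infection status with being on or off the antiviral drug, so it would tend to show a fall even if cure changes nothing

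*Protocol article*

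**What the plan says.** The last sentence of the healthcare-process paragraph in Endpoints and measures plans a before-after comparison of daily functioning, symptoms, quality of life and adverse events. For the last of these it covers "frequency of adverse events during active infection and once cured will be performed".

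Other sections fix the timing and the source of the events:

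- The Monitoring section gives a treatment period of 8–12 weeks, depending on the drug.
- Endpoints and measures: "To assess cure, HCV viral load will be determined 8–12 weeks after the end of treatment".
- Ethics: the gastroenterology service monitors adverse events as part of routine care, "in accordance with the effects described in the technical sheet of the medication prescribed to each patient".
- The end-of-treatment evaluation in Monitoring records "occurrence of adverse effects or interactions, and number of visits and calls during the treatment period".
- Monitoring then states: "A third and final analysis of all study variables will be carried out six months after starting the treatment".

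Endpoints and measures also provides for recording adverse events or interactions that the patient or a family caregiver reports. For change over time, the Data analysis section names a within-group repeated-measures ANOVA. The article does not define when active infection starts or ends for this comparison.

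**The concern.** For functioning, symptoms and quality of life, infection status is at least a plausible reason for a change. Adverse events differ because many are effects of the drug itself. The drug is taken in one period and not in the other, so the comparison is at least partly on-drug against off-drug. A fall would then follow from stopping treatment and would say nothing about cure.

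What is at stake is a published secondary table that shows fewer adverse events after cure when its design favours that result. The randomised comparison and the two primary endpoints are not affected.

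**Working it through.** **Timing.** Count weeks from the first dose. Treatment ends at week 8 to 12. Cure is determined 8–12 weeks later, between week 8 + 8 = 16 and week 12 + 12 = 24. The final assessment, six months after starting treatment, falls at about week 26.

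- If the cured period starts when cure is determined, it is wholly off drug and lasts about 26 − 24 = 2 to 26 − 16 = 10 weeks.
- If it starts at the end of treatment, it is still wholly off drug and lasts about 26 − 12 = 14 to 26 − 8 = 18 weeks.

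On either definition, no drug exposure falls in the cured period. The length of that period changes a great deal with the definition, so raw counts would carry a further distortion whose direction depends on the choice. The calculation below uses rates, which sets that problem aside.

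**Rates with no effect of cure.** The protocol gives no figure for adverse events, so there is none to reproduce and every rate here is an assumption. Let

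- b = background events per patient-month, the same before and after cure (0.05 to 0.20);
- d = extra events per patient-month while on drug (0 to 0.20);
- t = treated months, where 8 weeks = 8/4.345 = 1.84 and 12 weeks = 12/4.345 = 2.76;
- u = untreated infected months counted as active infection (0 to 6). The Interventions section describes a significant delay before treatment in standard care but gives no length.

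The rate in active infection is b + d·t/(u + t). The rate once cured is b. The ratio of cured to active is b / [b + d·t/(u + t)].

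| b | d | weeks on drug | u | active rate | ratio |
|---|---|---|---|---|---|
| 0.05 | 0.20 | 12 | 0 | 0.250 | 0.20 |
| 0.05 | 0.20 | 12 | 6 | 0.113 | 0.44 |
| 0.10 | 0.10 | 12 | 0 | 0.200 | 0.50 |
| 0.10 | 0.10 | 12 | 3 | 0.148 | 0.68 |
| 0.10 | 0.10 | 12 | 6 | 0.132 | 0.76 |
| 0.20 | 0.05 | 12 | 0 | 0.250 | 0.80 |
| 0.20 | 0.05 | 8 | 6 | 0.212 | 0.94 |
| any | 0 | 8 or 12 | any | b | 1.00 |

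For the third row: 0.10 / (0.10 + 0.10 × 2.76/2.76) = 0.10/0.20 = 0.50. With six untreated months: 0.10 / (0.10 + 0.10 × 2.76/8.76) = 0.10/0.132 = 0.76.

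Across the assumed range the null ratio is below 1 whenever d is above zero. Untreated infected time pulls it towards 1 but does not reach 1.

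**The other reading.** Suppose active infection means only the pre-treatment baseline, as the Discussion does for symptoms. Then neither period is on drug. But the article describes no collection of adverse events before treatment, and effects listed for a drug cannot occur before it is taken. The first side of the comparison would have no described data.

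**The case against.** The strongest reply is that the article only announces a comparison. A reader might infer that a fall in adverse events will be credited to cure, but no sentence says so. The one causal reading, in the Discussion, concerns negative symptoms that persist. This stands: the fault lies in what the contrast can show, and attribution to cure is not a stated intention.

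The definition of the periods may also sit in the full protocol or analysis plan. That is fair, and the missing definition is not itself the complaint. Neither available definition rescues the contrast: one is confounded with drug exposure and the other has no described data.

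The effect may be small. The Background describes antivirals with "proven efficacy in the general population and very limited side effects have been approved", and events reported by patients and caregivers are broader than the drug's listed effects. Both points stand. A reader might expect adverse events almost to vanish after cure, but that would require only drug-listed effects to count and none to occur off drug, which the collection rules do not support.

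Three further inferences go beyond the text:

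- *That the trial would have no safety comparison between arms.* The end-of-treatment evaluation covers all patients, and Data analysis plans between-group tests with patients analysed as allocated, so such a comparison is available.
- *That events heard at extra navigator contacts would be pooled and make that arm look less safe.* The statement that "scheduled and unscheduled visits led by the monitoring team and number of calls made and received by this team will be recorded" describes process indicators; nothing names those contacts as a pooled source of events.
- *That patients who stopped and were not cured appear only in the first period.* The article does not say who enters each side, and the contrast could be confined to patients who were cured.

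**Conclusion.** The point holds as a fault in one stated secondary comparison. If active infection includes the treated weeks, the comparison confounds infection status with drug exposure and leans towards a fall. If it means only the pre-treatment baseline, the comparison is empty.

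The direction rests on two things: the drug causes some events, and the background rate is the same in both periods under the null. The size cannot be fixed from the documents. The range of about 0.20 to 0.94 reflects assumed rates and assumed untreated time, and the mild end is as compatible with the text as the strong end.

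Importance is low to moderate. The primary endpoints, the sample size and the randomised comparison are unaffected.

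**What to change.** In Endpoints and measures, remove adverse events from the active-infection versus cured comparison, and leave functioning, symptoms and quality of life in it. Add a sentence to this effect: *Adverse events will be reported by randomised arm, as the proportion of patients with at least one event and as the number of events per patient-week on antiviral treatment.*

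Both measures are needed. If navigation leads more patients to take the drug, the proportion with an event could rise for that reason alone, and the rate allows for exposure. The rate exists only for patients who start treatment, so it should be read as descriptive.

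The between-arm count should not be limited to the common evaluation visits, because that would discard events found by the gastroenterology service's monitoring.

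The cost is a change of wording plus treatment start and stop dates for the denominator, which hospital pharmacy dispensing should help to supply. The before-after adverse-event table is lost. Treatment, visits and the primary analysis do not change.

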#### Data collection

Screening for HCV will be performed at the annual somatic control of SMD patients performed by mental health nurses. In the case of the Hospitalization Unit, HCV-positive cases will be extracted from hospital admission records. Detection will be done through blood tests including HCV testing. In case the virus is detected, part of the same blood sample will be used to perform the viral load test. Verbal consent will be requested from the patient or their legal representative prior to laboratory analysis. The patient will be informed that, in the event of a positive HCV and viral load test, they will be offered to participate in the study.

Patients will be randomized using a computer-generated sequence hidden from study participants and only known to a team member who will not participate in sample collection. Subjects will be included sequentially and assigned to the corresponding group through an online consultation system each time a new participant is ready to enter.

#### Interventions

In this study, a navigation program led by mental health nurses and auxiliary nurse technicians from a mental health unit will be implemented.

The control group will receive the standard of care. Patients in this group will be directly referred to their family physician with a report showing a positive HCV and viral load test for prescription of the standard treatment established by the Andalusian Health System. Standard management involves referral to the gastroenterologist, with a significant delay. Generally, the gastroenterologist prescribes a series of tests to confirm diagnosis. These tests will be performed in other units, for which previous appointment is required. Once test results become available, the patient will have another consultation with the gastroenterologist, who will finally establish a diagnosis and prescribe the treatment. The prescribed drug will be dispensed at the hospital pharmacy once a month until the treatment is completed, and cure is confirmed. The last phase of the treatment involves a final visit with the gastroenterologist to confirm that the viral load has disappeared according to a laboratory test.

In the intervention group, patients will be accompanied throughout the evaluation and treatment process until they are fully cured. The details of the intervention are described following the template for intervention description and replication (TIDiER). Follow-up will include a simplification of the clinical pathway of treatment. This way, the mental health service refers the patient to a first visit with the gastroenterologist. To guarantee compliance, all patients will be accompanied to that appointment either by a competent available family caregiver or by a member of the NNP team.

In the first visit, the gastroenterologist will perform a liver ultrasound and determine the most appropriate treatment for each patient. In the same visit, the patient will receive the prescribed pharmacological treatment, which will be dispensed at the hospital pharmacy. Thus, the patient obtains a final diagnosis and his pharmacological treatment the same day following a single-step clinical pathway.

The mental health nurse team will subsequently arrange for the analysis of the genotype of the virus in the mental health service, if necessary.

The intervention is based on an *ad-hoc* decision algorithm developed by all the healthcare services involved (See Fig. 1).

**Fig. 1 Fig1:**
[figure not shown]
Clinical route scheme hepatitis C in SMD patient

#### Monitoring

During the treatment period (8–12 weeks depending on the prescribed drug), actions will be taken to ensure correct treatment adherence. To such purpose, the mental health nurse will assess patient’s ability to comply with the treatment. In case of patient’s inability, the nurse will assess family’s commitment to supervise and remind the patient about drug intake. In both cases, the nurse will carry out an educational intervention to ensure that the patient and/or their family clearly understand treatment guidelines. This intervention is structured through a standardized care plan. In cases in which proper treatment use is not guaranteed, medication will be provided weekly by the monitoring team.

Upon completion of the 8–12 weeks treatment period, a final evaluation of all patients will be performed. The data collected in this evaluation visit include adherence to treatment, person responsible for treatment administration, occurrence of adverse effects or interactions, and number of visits and calls during the treatment period.

A third and final analysis of all study variables will be carried out six months after starting the treatment. Finally, disappearance of the viral load and, therefore, cure from HCV will be determined by a new blood test.

#### Ethics

This study was approved by the Malaga Provincial Research Ethics Committee with the code CQG-20 (0444-N-20). This study will comply with best clinical practice guidelines and the ethical standards for research involving human participants established in the Declaration of Helsinki and its subsequent versions.

Clinical data will be processed in accordance with current legislation on data protection.

In the preliminary phase of the study, consisting of a screening of the entire population diagnosed with a serious mental disorder, only verbal consent is being requested. This blood analysis has been included as part of the annual physical health review offered to patients with severe mental disorders in the Unit, which already involves blood extraction, and the Ethics Committee has approved that written consent is not required when treating of a screening of the entire population.

However, people who finally have a positive viral load (which will predictably be a small percentage of the previous ones) will be offered to participate in the clinical trial, for which they must give their informed consent in writing.

Prior to inclusion in the trial, each subject will be informed in writing and orally of the objectives and methodology of the project. Informed consent will be required for inclusion. If the patient is not legally competent, informed consent from the legal guardian will be required by nursing staff.

Adequate medical assistance will be provided in case patients experienced any adverse event. All patients will be informed of the need for medical assistance for concomitant illnesses of which the research team is aware.

The occurrence of adverse events will be monitored during the study by the Gastroenterology Service (Ward) as part of routine monitoring of HCV patients, in accordance with the effects described in the technical sheet of the medication prescribed to each patient.

In case of occurrence of a serious adverse event, expected or not, related or not to the study, the study will be temporarily suspended. Then, the event will be reported to the Ethics Committee and an audit procedure of the case will be arbitrated to determine the causal chain of the event and the possible factors involved. Urgent measures will be adopted to guarantee patient safety. If it is determined that the event is not related to the study, the latter will be resumed following Ethics Committee authorization. Otherwise, the study will be permanently suspended.

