### Background

The scientific literature shows a well-established association between the presence of SMD, such as schizophrenia, and poor physical health, especially in young people [10]. As compared to the general population, life expectancy in women and men with schizophrenia is 15 and 20 years lower, respectively [2]. Around a fifth of premature deaths are associated with suicide and accidents, but most are caused by physical illnesses [11], including, among others, infectious diseases such as HIV and hepatitis [12, 13]. Moreover, the risk of death from infectious disease is almost ten times higher in people with psychosis and schizophrenia, than in the general population [14].

There is evidence that patients with SMD are at an increased risk for HIV, HBV and HCV infection, as compared to the general population [15]. Generally, patients with a psychiatric illness are less aware of the transmission of infectious diseases and protective measures [16]. Risk sexual behaviours, low quality of life, or long-term hospitalization may contribute to higher infection rates in this population [15].

The prevalence of HCV infection among psychiatric patients has not been clearly established in Spain. Previous studies report a prevalence of HCV 2 to 16 times higher in SMD patients than in the general population [17–19].

Although HCV remains virtually asymptomatic in many cases, patients with chronic infection experience a variety of symptoms that include depression, fatigue, and neurocognitive deficit, which affect their quality of life [20]. Likewise, patients with SMD are generally on treatment with neuroleptic or stabilizer drugs, which cause dejection, tiredness, and anhedonia. In addition, since SMD causes similar symptoms, this symptomatology will be rarely attributed to a physical health problem such as HCV [12].

As a result, HCV is frequently underdiagnosed and untreated in patients with SMD [6], mainly due to the side effects of interferon, the only treatment available until a few years ago. Several clinical studies reveal that immunomodulatory treatment with interferon causes numerous physical and mental side effects, mainly symptoms of depression, anxiety, psychosis, and other non-specific symptoms such as fatigue, irritability, sleep disturbances, psychomotor retardation, decreased libido, insomnia, and/or cognitive impairment [21–25]. These side effects cause this population to poorly tolerate HCV treatment.

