##### Sample

As far as we know, there are no comparative studies assessing adherence of SMD patients to HCV treatment. For this reason, adherence to lifelong treatments such as oral antidiabetics in patients with schizophrenia has been taken as a reference. Based on data from Kreyenbuhl et al. [38], in which differences in adherence of patients with schizophrenia reached 10%, with an alpha of 0.05, a beta of 20%, and raising the threshold of differences to 15% because, unlike oral antidiabetics, it is a temporary treatment, the needed sample would be 276, assuming that adherence will be 80% in the intervention group and 65% in the control group. This sample will be increased by 15% to cover losses. Additionally, we considered the adherence threshold obtained by Ho et al. in their pilot non-controlled study for patients with HCV and psychiatric disorders, [39] with the same estimation parameters, resulting in a similar sample size.

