	Autonomous life	Concurrent validity, this scale was compared with the social behaviour schedule SBS: 0.46 Interrater reliability *r* = 0.76, and internal consistency α = 0.80
**Positive and Negative Syndrome Scale (PANSS)** [43]	Positive symptoms	Concurrent validity, it was compared with the Andreasen positive scale, *r* = 0.70 Interrater reliability ICC = 0.72, and internal consistency α = 0.62
	Negative symptoms	Concurrent validity, it was compared with the Andreasen negative scale, *r* = 0. 81 Interrater reliability ICC = 0.80, and internal consistency α = 0.92
	General psychopathology	Interrater reliability ICC = 0.56, and internal consistency α = 0.55
**EuroQol 5D** [45]	Mobility Self-care Usual activities Pain/ Discomfort Anxiety/Depression	Concurrent validity, it was compared with the SF-6D, *r* = 0.73 [46] Construct validity it was evaluated in spanish population

Sociodemographic (age, sex) and socioeconomic data (job performance), where applicable, will be assessed using the Social Class Classification of the Spanish Society of Epidemiology (if the patient does not have a job, it will be recorded whether the patient is in a situation of retirement, unemployment, temporary disability, or job search). Consumption of drugs of abuse, regular psychiatric treatment, physical comorbidities, and their treatment, as well as type of diagnosis, time from disorder onset, availability of family support, and mental health hospital admissions in the last 12 months will also be recorded. Other data to be collected include adverse events or interactions reported by the patient or family caregiver and other important observations collected during evaluation and follow-up visits.

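### One serious adverse event of any cause suspends the whole trial, and one event not shown to be unrelated ends it for good, with no comparison between arms

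*Protocol article*

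**What the plan says.** The rule is in the last part of the Ethics section and has three steps.

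- Trigger: "In case of occurrence of a serious adverse event, expected or not, related or not to the study, the study will be temporarily suspended". The event is then reported to the Ethics Committee and audited for its causal chain.
- Resumption: "If it is determined that the event is not related to the study, the latter will be resumed following Ethics Committee authorization".
- Every other outcome: "Otherwise, the study will be permanently suspended".

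The same section promises urgent measures for patient safety and medical assistance for adverse events. It places adverse-event monitoring with the gastroenterology service, against the product information of the prescribed drug.

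Other sections bear on how the rule works in practice. Interventions has patients in the programme accompanied from assessment through to cure. Monitoring adds: "In cases in which proper treatment use is not guaranteed, medication will be provided weekly by the monitoring team". Endpoints and measures fixes adherence by recall over the four days before interview, and cure by a viral load 8–12 weeks after treatment ends. Monitoring places the last assessment six months after treatment starts. Sample plans 276 patients plus 15% for losses.

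**The concern.** The trigger ignores causality and expectedness, and the permanent stop needs only one event. There is no count, no threshold, no comparison between arms and no middle course such as continuing with changes. The last sentence of the rule takes in everything not positively cleared, so it covers undetermined causality as well as expected, related events. The text gives the Ethics Committee a role in authorising resumption after an unrelated event, but no discretion in any other case.

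Because relatedness to the study is undefined, a reaction to the antiviral or an event of the underlying illness could be counted or not, depending on the reader. The article itself describes a population with raised suicide rates and shortened life expectancy (Introduction), and of its early deaths says: "Around a fifth of premature deaths are associated with suicide and accidents, but most are caused by physical illnesses". Serious events unconnected with a nurse navigation programme are foreseeable.

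At stake is whether the trial can answer its question. A permanent stop after one event, possibly in a control patient, says nothing about the programme. A temporary stop affects every patient then on study, not only the one with the event, and its length is not bounded.

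**Working it through.** **1. Planned size.** Sample states that "the needed sample would be 276, assuming that adherence will be 80% in the intervention group and 65% in the control group", with alpha 0.05 and 80% power. With a two-sided test, 1:1 allocation, pooled variance and no continuity correction:

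n per arm = [1.960·√(2·0.725·0.275) + 0.842·√(0.80·0.20 + 0.65·0.35)]² / 0.15² = (1.238 + 0.524)² / 0.0225 ≈ 137.9, so 138 per arm and 276 in total.

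The plan's figure reproduces exactly. Adding 15% gives 276 × 1.15 = 317.4, about 318. Dividing by 0.85 would give 325, which changes little below.

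**2. How many patients might have a serious event.** The article gives no rate, so p, the six-month risk per patient, is an assumption. With N = 318 and independent patients, P(at least one) = 1 − (1 − p)^N and P(two or more) = 1 − (1 − p)^N − N·p·(1 − p)^(N−1).

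| Assumed p | Expected patients affected | P(at least one) | P(two or more) |
|---|---|---|---|
| 0.5% | 1.6 | 0.80 | 0.47 |
| 1% | 3.2 | 0.96 | 0.83 |
| 2% | 6.4 | 0.998 | 0.99 |

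These are patients affected if the trial ran to full size. They are not a count of suspensions: an event during a suspension starts no new one, and a permanent stop cuts the series short.

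**3. Chance of a permanent stop.** Let r be the assumed per-patient risk of an event that is not cleared as unrelated. It is the serious-event risk multiplied by the chance that such an event is not cleared. P(permanent stop) = 1 − (1 − r)^318.

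| Assumed r | One way to reach it | P(permanent stop) |
|---|---|---|
| 0.05% | 5% risk × 1% not cleared | 15% |
| 0.1% | 10% × 1% | 27% |
| 0.5% | 5% × 10% | 80% |
| 1% | 10% × 10% | 96% |

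That one event is enough to end the trial needs no rate. It follows from the wording.

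**4. The rule beside the other sections.** Ethics suspends the study as a whole. Interventions and Monitoring make accompaniment and, where needed, weekly supply part of the programme during an 8–12 week course. Endpoints and measures ties adherence to a four-day recall and cure to a dated viral load. Ethics does not say whether that support continues during a suspension, or whether these assessments are still made on time.

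**The case against.** The rule is deliberately cautious and belongs to a study that an Ethics Committee approved. It contradicts no other section outright and biases no stated analysis. Several stronger readings are tempting, and the document does not support them.

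- A reader might infer that the trial will certainly be halted again and again. No event rate is given. That "mental health hospital admissions in the last 12 months will also be recorded" shows only that a variable is collected, not that admissions are frequent. The statement on causes of premature death gives their distribution, not a six-month risk. Population excludes patients with active symptoms that might affect participation until they are stable, which should lower early psychiatric events. Since monitoring follows the drug's product information, it is unclear whether a psychiatric admission would reach the trigger at all.
- A reader might infer that patients lose navigation support during a suspension. Ethics does not say so. It promises safety measures, and the Discussion says the Unit's own staff deliver the programme, so support could continue. The sound point is ambiguity.
- A reader might infer that a known antiviral reaction in a control patient must end the trial. It could equally be attributed to standard care and so cleared. Both readings are open because relatedness is undefined.

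These objections limit the claim about frequency and harm. They do not touch the core: the wording allows one uncleared event in either arm to end the trial, and nothing elsewhere in the article softens it. Ethics approval does not remove this, because the text leaves the Committee no choice once an event is not cleared.

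**Conclusion.** The concern holds as a defect in a rule that the article states in full, not as a gap left to another document. The trial can be ended by one event in either arm, or by failure to establish a cause, without any evidence about the programme.

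The probability of that outcome runs from about 15% to 96% over the assumed range of 0.05% to 1% uncleared-event risk per patient. Repeated serious events are about an even chance at a 0.5% risk and likely from about 1% upward. These figures rest on assumed rates, full recruitment of about 318 and independence between patients. They show how sensitive the trial is to the rule and do not forecast what will happen. Effects on support and on assessment timing are unresolved questions in the text, not established harms.

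**What to change.** Amend the rule in the Ethics section so that:

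- every serious event is still reported at once to the Ethics Committee;
- causality to the trial's own procedures, as distinct from the antiviral and the underlying illness, is assessed before any halt of the whole study;
- permanent termination is an Ethics Committee decision on the accumulated events by arm, not the automatic result of one event or of undetermined causality.

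Reconcile the rule with Interventions, Monitoring, and Endpoints and measures: state what continues during a pause, and how the adherence and viral-load assessments are kept in their windows. The exact safety triggers and the care of patients on treatment are for the investigators and the Ethics Committee to set.

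The cost is one amended paragraph and the Committee's agreement. The downside should be stated openly: unrelated events, and some expected or drug-related ones, would no longer stop the study automatically. Immediate reporting of all of them remains.
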